### **8.2 Analysis principles**

- 1) For the primary outcome assessed at two levels (mild-to-moderate and severe flares), Bonferroni correction was used and two-sided at a significance level of 0.025. Other tests were performed two-sided at the significance level of 0.05. The confidence level for all confidence intervals (CI) will be 95%.
- 2) The number of observations used in the analysis will be reported.
- 3) The statistical analysis plan is drafted prior to database lock, and it includes a detailed description of the statistical analyses. The statistical analyses were performed using SPSS Statistics (version 23.0), GraphPad Prism (version 8.0), and R software

(version 4.0.0). Figures will be plotted using GraphPad Prism (version 8.0) and R software (version 4.0.0).

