### **8.5 Primary outcome**

Flare proportion was defined as categorical variables, data were expressed in the form of frequency (percentages). The primary outcome was the proportion of patients with flares (including mild-to-moderate flares and severe flares) during follow-up. Safety of Estrogens in Lupus Erythematosus National Assessment-Systemic Lupus Erythematosus Disease Activity Index (SELENA-SLEDAI) Flare Index (SFI) was used for assessing disease flares in this trial. Pearson Chi-square or Fisher's exact tests were used to compare between-group differences. We first calculated the total flare rate, and then calculated mild-to-moderate flare rate and severe flare rate, respectively.

For the primary outcome, Bonferroni correction was used and two-sided at a significance level of 0.025. A more stringent statistical criterion was used. Relative risk (RR) was employed to compare the proportion of patients with the end point between MMF group and Control group. Severe flare-free survival proportion was estimated by using the Kaplan-Meier method in the intention to MMF group and Control group with a log rank test. Regarding patients who dropped out of the study, we collected all of the data during follow-up period. For patient who loss to follow-up, we did not collect the data for the subsequent time after lost to follow-up event. We used the ITT set for primary outcome calculation. All of the patients were included in the denominator. We estimated the severe flare-free survival proportion of the MMF group and Control group in both ITT and PP Set using the Kaplan-Meier method.

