**Table 3 Outcomes of 96-week follow-ups.**

|  | Control group | MMF group | RR | P value |
|--|---------------|-----------|----|----------------|
|  |               |           |    |                |

|                                            | (n=)                  | (n=)                  |          |
|--------------------------------------------|-----------------------|-----------------------|----------|
|                                            | Mean (SD) or
N (%) | Mean (SD) or
N (%) | (95% CI) |
| Primary outcome, %                  |                       |                       |          |
| Proportion of severe flares                |                       |                       |          |
| Proportion of mild to moderate flares      |                       |                       |          |
| Severe flares, %                    |                       |                       |          |
| Lupus nephritis                            |                       |                       |          |
| Neuropsychiatric symptoms                  |                       |                       |          |
| Rash (prednisone dose > 0.5mg/kg/day)      |                       |                       |          |
| Pleurisy                                   |                       |                       |          |
| Thrombocytopenia (<60* 10  /L) |                       |                       |          |
| Pulmonary arterial hypertension            |                       |                       |          |
| Hemolytic anemia                           |                       |                       |          |
| Fever (prednisone dose > 0.5mg/kg/day)     |                       |                       |          |
| Henoch-Schonlein purpura                   |                       |                       |          |
| Moderate mitral insufficiency              |                       |                       |          |
| Arthritis (prednisone dose > 0.5mg/kg/day) |                       |                       |          |

**Mild to moderate flares,  
%**

Arthritis

Rash

Oral ulcer

Fever

Leukopenia  
( $1.5-4 \times 10^9/L$ )

Thrombocytopenia  
( $60-100 \times 10^9/L$ )

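### The plan does not settle which flare comparison is the primary test or at what alpha, so control of family-wise error is not shown and the stated 80% power may not apply

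*Combined protocol and SAP*

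**What the plan says.** The statements about the primary comparison do not agree.

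- **Definition.** SAP 8.5: "The primary outcome was the proportion of patients with flares (including mild-to-moderate flares and severe flares) during follow-up". SAP 3.1 and protocol 9.1 define the outcome the same way, as one proportion covering both severities.
- **Sample size.** SAP 6 and protocol 5.3 use one comparison, 10% on MMF against 30% on control, at a two-sided 0.05. This gives 58 per group, and 65 after 10% drop-out.
- **Tests.** SAP 8.5: "Pearson Chi-square or Fisher's exact tests were used to compare between-group differences". The next sentence is "We first calculated the total flare rate, and then calculated mild-to-moderate flare rate and severe flare rate, respectively".
- **Alpha.** SAP 8.5: "For the primary outcome, Bonferroni correction was used and two-sided at a significance level of 0.025". SAP 8.2 gives the reason: "For the primary outcome assessed at two levels (mild-to-moderate and severe flares), Bonferroni correction was used"; all other tests are at 0.05. Protocol 10.2 agrees with SAP 8.2. Protocol 10.1 puts every test at 5%.
- **Results table.** Under the primary outcome, SAP Table 3 has a row for "Proportion of severe flares" and one for mild-to-moderate flares. It has none for total flare.
- **Intervals.** SAP 8.2: "The confidence level for all confidence intervals (CI) will be 95"%. Table 3 prints the relative risk with its 95% CI beside the P value.

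Neither document says which comparison decides the trial, whether one significant result is enough, or whether calculating the total first makes it a gate for the other two.

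**The concern.** Total flare is the outcome that was defined and powered. As written, it could be tested at 0.025 (SAP 8.5), at 0.05 as one of the other tests (SAP 8.2), or not reported as a primary result at all (Table 3). The two severity levels could be the whole primary family or follow-up analyses.

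Three things depend on the answer. The first is the chance of a false positive claim, which has to be fixed before the data are seen. The second is power, because the sample size assumes 0.05. The third is reporting, because a 95% CI beside a 0.025 test gives opposite messages for many results with p between 0.025 and 0.05.

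**Working it through.** **1. Reproduce the plan's sample size.** Inputs from SAP 6: p1 = 0.10, p2 = 0.30, two-sided alpha 0.05, unpooled Z test.

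Closed form: n = (1.960 + 0.842)² × (0.10×0.90 + 0.30×0.70) / 0.20² = 7.85 × 0.30 / 0.04 = 58.9, so 59. Exact binomial enumeration at n = 58 gives power 0.8036 and actual alpha 0.0568 (common rate 30%), both matching the plan. Drop-out: 58 / 0.90 = 64.4, so 65. The figure reproduces, but only for one test at 0.05.

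**2. Power if 0.025 applies to total flare.** The critical value rises from 1.960 to 2.241. Hand check for the unpooled Z at n = 58: SE = √(0.30/58) = 0.0719 and 0.20/0.0719 = 2.781. Power is then about Φ(2.781 − 1.960) = 79.4% at 0.05 and Φ(2.781 − 2.241) = 70.5% at 0.025. Exact enumeration gives:

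| Test, n per group | alpha 0.05 | alpha 0.025 |
|---|---|---|
| Unpooled Z, 58 | 80.4% | 71.0% |
| Chi-square, 58 | 79.7% | 69.9% |
| Chi-square, 65 | 83.2% | 75.4% |

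The last row applies if all 65 per group count, as SAP 8.5 implies by keeping all patients in the denominator. Restoring 80% at 0.025 needs 72 evaluable per group (unpooled) or 75 (pooled). With 10% drop-out that is 72/0.90 = 80 or 75/0.90 = 83.3, so 84.

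**3. Family-wise error under each reading.** Bounds:

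- Two levels at 0.025: 2 × 0.025 = 0.05.
- Total flare as the sole primary test, or as a gate, at 0.05: 0.05.
- Any of three tests at 0.025: 3 × 0.025 = 0.075 (0.0731 if independent).
- Total at 0.05 plus two levels at 0.025, any one sufficient: 0.05 + 2 × 0.025 = 0.10.

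The tests are correlated because total flare is the union of the two levels, so actual error is below the last two bounds. The documents give no flare rates by severity, so the splits below are assumptions, with each patient counted at one level only. Simulation used 65 per group, no treatment effect, chi-square tests and 400,000 trials per row:

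| Severe / mild-to-moderate | Three tests at 0.025 | Total at 0.05, levels at 0.025 |
|---|---|---|
| 10% / 20% | 6.13% | 8.16% |
| 15% / 15% | 6.16% | 8.17% |
| 5% / 25% | 5.64% | 7.65% |
| 15% / 45% | 6.38% | 8.48% |

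The two levels alone at 0.025 give 4.5-4.9%. A wider set at 58 to 65 per group, including patients with flares at both levels, gives 5.6-6.6% for three tests at 0.025.

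**4. Interval against test.** Take 9 of 65 against 19 of 65.

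- Chi-square: pooled rate 28/130 = 0.215; z = (10/65) / √(0.215 × 0.785 × 2/65) = 0.1538/0.0721 = 2.13; p = 0.033, not significant at 0.025.
- RR = 9/19 = 0.47. SE of log RR = √(1/9 − 1/65 + 1/19 − 1/65) = 0.365.
- 95% CI (1.960): 0.23 to 0.97, which excludes 1.
- 97.5% CI (2.241): 0.21 to 1.07, which includes 1.

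**The case against.** A reader might infer that the error rate exceeds 5%. The documents do not support that as a plain statement. It needs all three comparisons to be confirmatory and any one of them to be enough, and no section says so. SAP 8.5 says the rates are calculated, the total first. SAP 8.2 and protocol 10.2 name two levels as the corrected family, and Table 3 shows those two. On that reading the nominal rate is 5%, and it is also 5% if total flare is the sole primary test or a gate.

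Even under the any-of-three reading the excess is small. A single chi-square test of total flare at 0.05 itself runs at about 5.2% with 65 per group, so 5.6-6.4% is roughly 0.5 to 1.2 points more. The figures near 8% need total flare at 0.05, while the power loss needs it at 0.025. Both cannot apply together, and SAP 8.5 sits closer to 0.025.

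Three further points are fair. Protocol 10.1 is a general section that 10.2 may be meant to override. The Bonferroni split does buy something if the sponsor wants a claim on either level. The interval mismatch concerns reporting and does not change the error rate.

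These points limit the size of the problem but do not remove it. The outcome definition and sample size point to one composite test, while the correction and results table point to two component tests. Nothing in the documents rules out choosing between them after the results are known.

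**Conclusion.** The primary test and its alpha are stated inconsistently. This follows from the text alone and needs no simulation. Family-wise error is not shown to be controlled, which is weaker than saying it is exceeded: it is a nominal 5% under several readings, and at most 7.5% (about 5.6-6.4% simulated at 65 per group) if any of three tests at 0.025 can win. The simulated range rests on assumed, mutually exclusive severity splits.

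If SAP 8.5 means total flare is tested at 0.025, the stated 80% power does not hold. It falls by about 9 to 10 points at 58 per group and about 8 points at 65, taking the plan's own 10% and 30%. The clash between 95% intervals and a 0.025 test arises whenever 0.025 is used for a primary comparison. This must be fixed, because the documents do not determine what result makes the trial positive.

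**What to change.** In SAP 8.2 and 8.5 and protocol 10.1 and 10.2, name total flare by week 96 as the sole primary test, at two-sided 0.05 with a 95% CI. This matches the outcome definition and the sample-size basis. Only if it is significant, test severe flare and then mild-to-moderate flare at 0.05 in that fixed order, or the pair by Holm. Add a total-flare row to Table 3 under the primary outcome.

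If the Bonferroni split is kept, state which tests are confirmatory and divide alpha by their number. Report intervals at the matching level (97.5% for 0.025), restate the power at that alpha, and bring protocol 10.1 into line.

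The first option costs wording and one table row. Its downside is that a claim about one severity level then requires the total-flare test to succeed first.

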## **6. Sample size calculation**

We referred to the flare rate of the placebo arm in 'Met Lupus' trial and the flare rate from the BLISS-52, BLISS-76 and BLISS-North East Asia phase III trials. We supposed the flare rate to be 10% in MMF group and 30% in Control group. Z test with unpooled variance ( $\alpha=0.0568$ ,  $\beta=0.1964$ ,  $\text{power}=0.8036$ ) was used for

sample size calculation. A sample size of 58 patients per group would provide the trial with 80% power at a two-sided alpha error of 0.05 to detect a difference between the two groups using the software PASS version 11.0. Taking an estimated 10% drop-out into account, a sample size of 65 patients per group could fulfill the statistical requirement. The sample size was calculated using PASS version 11.0 software as follows:

| Two Independent Proportions (Null Case) Power Analysis                      |                         |                         |                                     |                                   |                     |                     |                 |                 |        |
|-----------------------------------------------------------------------------|-------------------------|-------------------------|-------------------------------------|-----------------------------------|---------------------|---------------------|-----------------|-----------------|--------|
| Numeric Results of Tests Based on the Difference: P1 - P2                   |                         |                         |                                     |                                   |                     |                     |                 |                 |        |
| H0: P1-P2=0. H1: P1-P2=D1<>0. Test Statistic: Z test with unpooled variance |                         |                         |                                     |                                   |                     |                     |                 |                 |        |
|                                                                             | Sample
Size
Grp 1 | Sample
Size
Grp 2 | Prop H1
Grp 1 or
Trtmnt
P1 | Prop
Grp 2 or
Control
P2 | Diff
if H0
D0 | Diff
if H1
D1 | Target
Alpha | Actual
Alpha | Beta   |

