## **8. Statistical procedures**

### **8.1 Randomization and masking**

Participants were randomly assigned (1:1) using blocks of four to receive either MMF (MMF group) or a control treatment (Control group). A statistician from the Clinical Trial Center of Ruijin Hospital, [name], who was masked to trial allocation generated the randomization sequences by a computer algorithm. Then, numbers were written on the cards and packed in sequentially numbered envelopes that were opened when the patients were enrolled. [name] assigned patients to different groups according to the number on the card. Assessors were masked to the group allocation. Eligible subjects were recruited from the Department of Rheumatology and Immunology of Ruijin Hospital and the Department of Rheumatology and Immunology of the other two clinical centers. Doctors were responsible for patient inclusion and regular follow-up assessments ([name], [name], [name], [name], and [name]). The assessment of patient flare was strictly based on the SELENA-SLEDAI Flare Index (including severe flare, and mild to moderate flare) rather than subjective decisions. Data analysts ([name] and [name]) were not involved in patient assessment and treatment, and they were masked to the group allocation.

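### Patients lost without a recorded flare stay in the primary denominator and so count as flare-free to week 96, which biases the RR if loss differs between arms and some flares fall after loss

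*Combined protocol and SAP*

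**What the plan says.** SAP 8.5 defines the primary outcome as the proportion of patients with any flare, mild-to-moderate or severe, during follow-up. It is analysed in the ITT set by chi-square or Fisher's exact test at 0.025, with a relative risk. On the denominator it says: "All of the patients were included in the denominator". On loss to follow-up it says: "we did not collect the data for the subsequent time after lost to follow-up event". For patients who dropped out in other ways, the same section says that data over the follow-up period were collected.

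Protocol 8.1 keeps patients who stop the study treatment under assessment for the remaining visits, and SAP 4 keeps severe-flare patients in follow-up. Protocol 8.2 is different: withdrawal ends both treatment and study participation, and nothing more is collected after consent is withdrawn.

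Kaplan-Meier is planned for severe flare only (protocol 10.2, SAP 8.4 and 8.5). The per-protocol set is used only for that curve. SAP 8.4 mentions a Cox model without naming its outcome. SAP 6 handles loss another way: "Taking an estimated 10% drop-out into account, a sample size of 65 patients per group could fulfill the statistical requirement", starting from 58 per group.

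**The concern.** Only a recorded flare can enter the numerator. If everyone stays in the denominator and nothing is observed after loss, a patient lost without a flare contributes a non-event for the whole 96 weeks. Scheduled visits are 24 weeks apart and the first is at week 24, so a dosed patient lost before then would count as 96 weeks flare-free with no scheduled post-baseline assessment.

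The rule lowers each arm's flare proportion according to that arm's own loss, so unequal loss moves the relative risk. Unequal loss is plausible here. There is no placebo, so patients know their arm. They buy their own drugs (protocol 7.2.1), so the MMF arm pays for one more. Protocol 2.4.1 links gastrointestinal and blood-count effects to MMF. At stake is the primary comparison itself, because the plan has no other analysis of the any-flare outcome that would reveal the problem.

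**Working it through.** **The plan's own figure.** The inputs from SAP 6 are "We supposed the flare rate to be 10% in MMF group and 30% in Control group", "Z test with unpooled variance", and 58 per group at two-sided 0.05. Exact binomial enumeration of that test gives power 0.8036, and actual alpha 0.0568 at a common rate of 30%. Both match the document. Then 58/0.90 = 64.4, rounded up to 65. The sample-size arithmetic is sound.

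**Model of the SAP 8.5 rule.** Let p be an arm's true 96-week flare risk, L its loss, and u the share of lost patients' flares that fall after loss. Assume that loss is unrelated to flare risk.

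- Observed proportion = p × (1 − L × u)
- Observed RR = true RR × (1 − L_MMF × u) / (1 − L_control × u)

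The values of L by arm and of u are assumptions; the documents give neither. The only loss figure is the 10% allowance in SAP 6.

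**No true effect: 30% in both arms, 65 per arm.** Rejection rates come from exact enumeration of the two-sided Pearson chi-square test.

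| Loss control / MMF | u | Observed control / MMF | RR | Rejects at 5% | Rejects at 2.5% | Of which for MMF, at 2.5% |
|---|---|---|---|---|---|---|
| 0 / 0 | – | 30.0% / 30.0% | 1.00 | 5.2% | 2.6% | 1.3% |
| 5% / 15% | 1 | 28.5% / 25.5% | 0.895 | 6.9% | 3.6% | 3.2% |
| 5% / 15% | 0.5 | 29.25% / 27.75% | 0.949 | 5.6% | 2.8% | 2.0% |
| 5% / 20% | 1 | 28.5% / 24.0% | 0.842 | 9.2% | 5.1% | 4.9% |
| 5% / 20% | 0.5 | 29.25% / 27.0% | 0.923 | about 6.1% | about 3.1% | 2.6% |

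For example, 0.30 × (1 − 0.20) = 0.240, 0.30 × (1 − 0.05) = 0.285, and 0.240/0.285 = 0.842. The 5% / 15% rows average to the planned 10%. The 5% / 20% rows put MMF loss at twice the plan.

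**Planned effect: 10% against 30%, true RR 0.333, u = 1.** With 15% lost on MMF and 5% on control, the observed rates are 8.5% and 28.5%, RR 0.298. With the losses reversed they are 9.5% and 25.5%, RR 0.373. Equal 10% loss gives 9% and 27%, and the RR stays at 0.333.

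**Does the conclusion depend on the rule?** Take 7 lost per arm (65 − 58) and, for illustration, 6 MMF and 17 control flares among the 58 completers in each arm, close to 10% and 30%.

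- Lost counted as flare-free: 6/65 against 17/65, RR 0.35, chi-square p = 0.011.
- Lost counted as flares in both arms: 13/65 against 24/65, RR 0.54, p = 0.033, which misses 0.025.
- Only lost MMF patients counted as flares, an extreme bound: 13/65 against 17/65, RR 0.76, p = 0.41.

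**Power.** By the chi-square test, 58 evaluable per arm at 10% against 30% gives 79.7% at 0.05 and 69.9% at 0.025. Sixty-five per arm at 9% against 27% gives 77.9% and 68.8%. The rule costs 79.7 − 77.9 = 1.8 points and 69.9 − 68.8 = 1.1 points.

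**The case against.** The strongest reply is that the documents confine the problem. Stopping treatment is not loss in this trial: protocol 8.1 keeps such patients under assessment, SAP 4 keeps following severe-flare patients, and SAP 8.5 says data were collected for those who dropped out. MMF intolerance would therefore often lead to stopping the drug rather than to missing flare status. Assessors and analysts are also described as masked. This stands, and it limits the point to patients lost to contact or withdrawn from the study, and among them to those with no flare recorded before loss.

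A reader might go further than the documents allow in four ways.

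- *That the SAP says lost patients are flare-free.* It does not. The scoring follows from its two rules taken together.
- *That any difference in loss biases the result, or that the bias favours MMF.* If every flare in lost patients precedes loss, there is no bias. More loss on control would work against MMF. At the planned effect with 15% MMF and 5% control loss, the risk difference stays at −0.20 although the RR moves.
- *That the 5% / 20% row with all flares after loss is the expected size.* It is the upper end of an assumed range.
- *That the rule is what brings power below 80%.* It costs 1 to 2 points. The rest of the fall to 68.8% comes from testing at 0.025 after planning at 0.05, which is a separate matter.

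It is also fair to say that censoring assumes non-informative loss, and that 24-week visits make flare times coarse. Those points shape the remedy but do not remove the need for one.

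**Conclusion.** The concern holds for patients lost to contact or withdrawn from the study without a recorded flare. SAP 8.5 in effect scores them as flare-free to week 96, and the plan contains no rule for unknown flare status, no any-flare analysis that censors at loss, and no sensitivity analysis for missing data. This is more than missing detail, because following the stated rules gives a biased RR when loss differs by arm and some flares fall after it.

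Over the unequal-loss scenarios tabulated, with no true effect, the RR lies between 0.84 and 0.95. The false-positive rate lies between 5.6% and 9.2% against a test size of 5.2%, and between 2.8% and 5.1% against 2.6%. These figures assume 30% risk in both arms, 65 per arm, and loss unrelated to flare risk. Equal loss leaves the RR unbiased under that last assumption, but could bias it if loss is related to flare risk. No claim is made about power, or about what loss in this trial was.

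**What to change.** In SAP 8.5, state that flare status after loss or withdrawal is unknown, and replace the primary estimate by one of two options:

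- the 96-week risk of first flare of any level in each arm, censored at the last assessed visit, by an interval-censored or visit-based method because visits are 24 weeks apart, with the difference and ratio of risks and their confidence intervals; or
- the 96-week proportion with flare status after loss multiply imputed.

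Report loss and withdrawal by arm and by visit. Add a prespecified best/worst-case or tipping-point table that varies the assumed flare risk of lost patients in each arm. Keep the present all-in-denominator proportion as a supportive analysis. State also whether the denominator is everyone randomised or the ITT set in SAP 7, which requires at least one dose.

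The cost is SAP wording and modest extra analysis on data already collected. The downside is an assumption that loss is non-informative, or missing at random, which the tipping-point table tests.
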